## Abstract

**Background:**

Australia has increased coverage of antiretroviral treatment (ART) over the past decade, reaching 73% uptake in 2014. While ART reduces AIDS-related deaths, accumulating evidence suggests that it could also bolster prevention efforts by reducing the risk of HIV transmission (‘treatment as prevention’). While promising, evidence of community-level impact of treatment as prevention on reducing HIV incidence among gay and bisexual men is limited. We describe a study protocol that aims to determine if scale up of testing and treatment for HIV leads to a reduction in community viraemia and, in turn, if this reduction is temporally associated with a reduction in HIV incidence among gay and bisexual men in Australia’s two most populous states.

**Methods:**

Over the period 2009 to 2017, we will establish two cohorts making use of clinical and laboratory data electronically extracted retrospectively and prospectively from 73 health services and laboratories in the states of New South Wales and Victoria. The ‘positive cohort’ will consist of approximately 13,000 gay and bisexual men (>90% of all people living with HIV). The ‘negative cohort’ will consist of at least 40,000 HIV-negative gay and bisexual men (approximately half of the total population). Within the negative cohort we will use standard repeat-testing methods to calculate annual HIV incidence. Community prevalence of viraemia will be defined as the proportion of men with a viral load ≥200RNA copies/mm^3^, which will combine viral load data from the positive cohort and viraemia estimates among those with an undiagnosed HIV infection. Using regression analyses and adjusting for behavioural and demographic factors associated with infection, we will assess the temporal association between the community prevalence of viraemia and the incidence of HIV infection. Further analyses will make use of these cohorts to assess incidence and predictors of treatment initiation, repeat HIV testing, and viral suppression.

**Discussion:**

This study will provide important information on whether ‘treatment as prevention’ is associated with a reduction in HIV incidence at a community level among gay and bisexual men.

## Background

Since 1996, combination antiretroviral therapy (ART) for HIV infection has been used to treat HIV by reducing the progression to AIDS and preventing AIDS-related deaths. In recent years, ART has been acknowledged as a key biomedical component in reducing onward HIV transmission. Known as ‘treatment as prevention’, the potential for this public health approach to control HIV transmission was evident in the landmark HIV Prevention Trials Network (052) randomised control trial, which in 2011 observed a 96% reduction in HIV transmission to heterosexual partners of HIV-positive individuals allocated to early ART compared with those with delayed therapy [1]. More recently, observational cohorts of both same and opposite sex couples have provided further supporting evidence, with no linked HIV transmissions among those with sustained viral suppression despite thousands of acts of condomless sex [2, 3]. These findings have formed the basis of international recommendations to employ treatment as prevention as an additional strategy to eliminate HIV [4].

For treatment as prevention to have greatest impact, HIV testing and treatment coverage must be high and treatment must be initiated soon after an infection is diagnosed [5]. National estimates from 2014 showed that 73% of people diagnosed with HIV in Australia were on ART [6] and observational research suggests that treatment coverage has increased over time [7]. Such increases in treatment coverage likely reflect changes to HIV treatment guidelines. While earlier guidelines only recommended ART initiation for people with CD4 cell count below 350 cells/mm^3^ in 2012 they were updated to include consideration for those with counts below 500 cells/mm^3^ and most recently recommended treatment initiation as soon as possible after diagnosis independent of CD4 cell count [8]. Additionally, a number of policy and structural barriers to HIV treatment were addressed, including the removal of CD4 cell count criteria for medication reimbursement through the national health scheme [9] and in the state of New South Wales the removal of upfront co-payments associated with treatment dispensing [10].

Alongside treatment, efforts have been made to increase HIV testing in Australia through a number large-scale health promotion campaigns and new initiatives to improve access to testing services. Community surveys of gay and bisexual men in 2014 found that 90% had ever received an HIV test with two-thirds tested within the previous year, proportions that have been generally stable over the past ten years [11]. Among men at highest risk of infection, Australian guidelines recommend at least six-monthly HIV testing [12] but clinical data show only about half of higher-risk men in 2014 returned for a follow-up test within six months (up from 40% in 2009) [13]. Thus, there have been some improvements in HIV testing among gay and bisexual men but to a lesser degree than for treatment.

Despite improvements in HIV treatment and testing coverage, annual HIV notifications in Australia increased by 22% between 2004 and 2012 [6]. In response, many Australian jurisdictions moved to expand ‘treatment as prevention’ initiatives and in 2014 all jurisdictional health ministers committed to a target of virtual HIV elimination by 2020. In recent years, there has been an increased focus on testing and treatment initiatives, implemented through partnerships between governments, clinicians, community organisations and researchers. These changes represent a major effort nationally to advance treatment as prevention.

This paper describes a study titled ‘TAIPAN’ (Treatment with Antiretrovirals and their Impact on Positive And Negative Men), which aims to establish two large longitudinal cohorts between 2009 and 2017 to evaluate if the scale up HIV testing and treatment leads to a reduction in community viraemia and if this reduction is temporally associated with a reduction in HIV incidence among gay and bisexual men.

## Methods

### Study design

This study will involve a longitudinal cohort design using de-identified, electronic medical records extracted for the period 1 January 2009 to 31 December 2017.

### Aims

The primary aim of the study is to determine the temporal association between the community prevalence of HIV viraemia and the incidence of HIV infection among gay and bisexual men at a community-level. The secondary aims are: i) to assess the association between changes in guidelines and policies and earlier uptake of HIV treatment among gay and bisexual men, ii) to identify incidence and predictors of repeat HIV testing among HIV negative gay and bisexual men, and iii) to identify incidence and predictors of supressed HIV viral load among HIV positive gay and bisexual men.

### Setting

Two study cohorts will be established in the two Australian states where approximately 65% of gay and bisexual men in Australia live: New South Wales (population ~7.6 million) and Victoria (population ~5.9 million).

### Cohorts

Study cohorts will be established using de-identified data extracted from electronic patient medical records. These data will be collected via an existing health sentinel surveillance network of clinics and laboratories known as the *Australian Collaboration for Coordinated Enhanced Sentinel Surveillance of Sexually Transmissible Infections and Blood Borne Viruses* (ACCESS). The existing network will be expanded from 50 health services and pathology laboratories in New South Wales and Victorian to a total of 73, including: 39 publicly-funded sexual health clinics, 10 general practice clinics with medium to high caseloads of gay and bisexual men (50 or more patients per year), six hospital HIV outpatient clinics, four community-led HIV testing services, and 14 private and public pathology laboratories.

Expansion of the surveillance network will aim to capture 95% or more of all HIV viral load tests conducted in both states as well as 100% of HIV diagnoses. These targets will be achieved by recruiting all laboratories that conduct HIV viral load testing as well all reference laboratories responsible for confirmatory HIV Western Blot testing. Table 1 outlines the service types and criteria used to identify health services and laboratories relevant to TAIPAN.

**Table 1 Tab1:** Health service and pathology laboratory types and criteria for the TAIPAN project (*n* = 73)

	Health services	Pathology laboratories
Service types	Sexual health clinics (*n* = 39) General practice clinics (*n* = 10) Hospitals (*n* = 6) Community-led health services (*n* = 4)	Publicly-funded (*n* = 6) Private (*n* = 8)
Criteria (any)	≥50 HIV gay/bisexual men annually ≥20 HIV positive male patients annually ≥5 HIV diagnoses annually	Any confirmatory HIV testing Any HIV viral load testing

### Participants

Using de-identified data extracted from ACCESS sites, two patient cohorts of gay and bisexual men will be established: one comprising HIV positive men (‘positive cohort’) and the other HIV negative men (‘negative cohort’). The positive cohort will consist of approximately 13,000 HIV positive gay and bisexual men (approximately 90% of all gay and bisexual men with HIV in both states) and the negative cohort will consist of at least 40,000 HIV negative gay and bisexual men (approximately half of the population).

Both cohorts will be limited to men aged 16 years and older for whom there is at least once record indicating a history of sexual contact with other men. Indicators of same sex contact can be behavioural (i.e., self-reporting same sex partners), identity-based (i.e., recorded sexual orientation as gay or bisexual), or procedural (i.e., collection of an anal swab for STI testing). The positive cohort will include patients recorded as HIV positive or those who receive an HIV diagnosis during the study period. The negative cohort will include patients whose first record of HIV testing during the study period is negative. If during the course of the study a person is diagnosed with HIV, they will be reclassified to the positive cohort. Follow-up during the study period will be based on records from the participating services as well as the pathology conducted by participating laboratories.

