The community prevalence of viraemia is defined as the proportion of gay and bisexual men (diagnosed and undiagnosed) with a viral load of ≥200 RNA copies/mm^3^. A viral load of ≥200 was selected as this is a commonly-used clinical marker of viral suppression and a recent meta-analysis found no transmission of HIV among individuals with less than 200 RNA copies/mm^3^ [14]. Community prevalence of viraemia was selected as it has been demonstrated to have the strongest correlation with HIV incidence over other measures (e.g., mean viral, treatment coverage) [15]. Our measure of viraemia will comprise the following four components:Annual prevalence of viraemia: will be calculated within the positive cohort using the annual prevalence of viral load test results of ≥200 RNA copies/mm^3^ (‘viraemia’) at each patients last viral load test within a calendar year. We will conduct sensitivity analyses to include any viral load test ≥200 RNA copies/mm^3^ in a year and also using a higher threshold of ≥1000 RNA copies/mm^3^.Annual prevalence of diagnosed HIV infection among gay and bisexual men: will be estimated using population prevalence techniques developed by and used for Australia’s national HIV surveillance [6]. This approach produces a prevalence estimate using data on HIV diagnoses from Australia’s National HIV Registry, adjusting for duplicate entries, deaths, and migration outside of Australia. For this estimate we will focus on HIV diagnoses where homosexual contact is identified as the route of transmission.Annual prevalence of undiagnosed HIV infection among gay and bisexual men: will be estimated using standard back-project models [16] and validated against a separate bio-behavioural survey conducted in 2013–2014 and to be repeated in 2017 [17].Prevalence of viraemia in gay and bisexual men with undiagnosed HIV infection: will be calculated using an estimate of undiagnosed infection obtained from the back-projection models coupled with the assumption that all undiagnosed men have viral loads of ≥200 RNA copies/mm^3^. We will also consider different viral load levels among undiagnosed men by using data from the National HIV Registry and stratifying viral load at diagnosis by HIV testing history (i.e., reported time since HIV test prior to diagnosis).

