**Fig. 1 Fig1:**
[figure not shown]
Method for calculating the prevalence of HIV viraemia among diagnosed and undiagnosed gay and bisexual men

#### Outcome 2

HIV incidence will be calculated using repeat testing among the negative cohort, [18] which will consider patients with two or more HIV tests for whom the first test was negative. We expect that more than 80% of gay and bisexual men will have at least two tests over the study period. An incident infection will be defined as an HIV diagnosis following a negative test and time at risk will be calculated as the time between each patient’s first and last test or a patient’s first test and HIV diagnosis. The number of incident infections will be divided by the person time (in years) at risk.

#### Outcome 3

Data from the positive cohort will also be used to calculate the incidence of ART initiation (i.e., the point at which ART is initiated) with the follow-up period defined as the time after HIV diagnosis (person years of infection). This variable will be restricted only to men diagnosed with HIV during the study period.

#### Outcome 4

Data from the negative cohort will be used to calculate the incidence of repeat diagnostic HIV testing. The incident event is defined as the point at which a patient achieves a second HIV test within six weeks to 12 months of a previous test, with follow-up time defined as the period between a patient’s first HIV test and last clinical encounter. Follow-up time will cease if a patient has no recorded service event of any kind within a two year period but will resume at the point of future service events (i.e., reengages with a participating service). Follow-up will also cease if a patient is diagnosed with HIV.

#### Outcome 5

Among the positive cohort, the incidence of viral suppression will be calculated. Viral suppression is defined as two consecutive viral load tests of <200 RNA copies/mm^3^ separated by at least three months; the first test will be taken as the point of suppression for calculating time. This variable will only be calculated among patients with no history of previous treatment and will exclude those for whom there is no or only one viral load test result. We will conduct a sensitivity analysis with a higher viral load threshold of <1000 RNA copies/mm^3^.

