### Covariates

Covariates considered for this study’s analyses will include patient demographic variables (area of residence, age, indigenous status, country of birth, if Australia’s public health insurance scheme ‘Medicare’ was recorded), clinical information (HIV status, STI diagnoses, CD4 cell count and viral load results, hepatitis B and C co-infection), behavioural information (gender(s) of sexual partner, condom use, injecting drug use, recent sex work, and sexual partner numbers) and service provision - related variables (clinic location - urban vs regional/remote, service type - general practice, sexual health clinic, hospital, community-led service). Additionally, treatment information and treatment type will be used to assess the use of HIV antiretrovirals among the negative cohort as pre- and/or post-exposure prophylaxis (‘PrEP’ and ‘PEP’). The only variables likely to be missing from a substantial number of records relate to sexual risk behaviour. For this information we will draw on records from multiple sources and use a recorded diagnosis of rectal chlamydia and gonorrhoea as a surrogate marker of risk [19]. Not all covariates will be relevant to every analysis.

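### Entry to the incidence analysis rests on an undated record of sex with men, while time at risk starts at the first HIV test, so eligibility can depend on information recorded at or after the outcome

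*Protocol article*

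**What the plan says.** Four statements in the protocol article bear on this point.

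- **Entry (Participants).** Both cohorts consist of men aged 16 or over "for whom there is at least once record indicating a history of sexual contact with other men". The record may be behavioural, identity-based or procedural (an anal swab), and any one is enough. No date is attached to it.
- **Negative cohort (Participants).** The only dated condition concerns the HIV test: "The negative cohort will include patients whose first record of HIV testing during the study period is negative". On diagnosis the man changes cohort: "If during the course of the study a person is diagnosed with HIV, they will be reclassified to the positive cohort".
- **Time at risk (Outcome 2).** "An incident infection will be defined as an HIV diagnosis following a negative test and time at risk will be calculated as the time between" the first and last test, or the first test and diagnosis. The clock does not wait for the first record of sex with men.
- **Completeness (Covariates).** "The only variables likely to be missing from a substantial number of records relate to sexual risk behaviour". No completeness figure is given for the eligibility indicator itself.

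The article neither restricts the indicator to records made before diagnosis nor plans a sensitivity analysis on it.

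**The concern.** Data are extracted partly in retrospect, so eligibility can be judged with later records in view. Take two men with a negative first test and no record of sex with men. One seroconverts, enters HIV care, and has the indicator recorded there; he comes in with his event and all his time since the first test. The other stays negative and unrecorded, and contributes nothing. Selection then depends on the outcome.

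There is an opposite effect. A man first recorded late in follow-up, while still negative, brings in his earlier time. Had he been diagnosed during that time with no record created, neither he nor his event would have counted. That stretch is event-free by construction and pulls the rate down.

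The quantity at stake is the outcome of the primary aim. The planned Poisson model adjusts for covariates among included men only, so it cannot restore men whom the rule excludes. If the net distortion differs between 2009–2011 and 2015–2017, it enters the trend that is to be related to viraemia.

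**Working it through.** **The plan's own figure, as a yardstick.** Sample size: 420 infections per year × 0.80 with a testing history = 336 incident cases per year. For a hazard ratio of 0.80 at two-sided 0.05 (sidedness assumed) and 80% power, the Schoenfeld formula needs 631 events over two years compared 1:1. With 336 + 0.8 × 336 = 604.8 events power is 78%; with 336 + 336 = 672 it is 82%. The statement reproduces and is not in dispute. The changes of interest are thus a 20% annual decline and an assumed overall reduction of 30%.

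**Step 1: level of incidence, ignoring when the record is made.** Let *s* be the probability that a man is recorded without a diagnosis, and *d* the probability that diagnosis creates the record in a man otherwise unrecorded. Both are assumed; the document gives neither.

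Observed / true incidence = [*s* + (1 − *s*)*d*] / *s*

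| *s* | *d* = 0.5 | *d* = 0.9 |
|---|---|---|
| 0.99 | 1.005 | 1.009 |
| 0.95 | 1.03 | 1.05 |
| 0.90 | 1.06 | 1.10 |
| 0.80 | 1.13 | 1.23 |
| 0.70 | 1.21 | 1.39 |

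This shortcut can only point upward, because it leaves out the event-free time described above.

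**Step 2: the same with timing.** Simulation with a true rate of 0.90 per 100 person-years, potential follow-up uniform from 0.5 to 9 years, a share of men recorded at the first test, and the rest recorded at a constant yearly rate while negative. All these inputs are assumptions. Incidence per 100 person-years under the any-time rule (simulation error about 0.01):

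| Recorded at first test; later yearly rate | *d* = 0 | *d* = 0.25 | *d* = 0.5 | *d* = 0.9 |
|---|---|---|---|---|
| 70%; 0.15 | 0.83 | 0.87 | 0.93 | 1.01 |
| 90%; 0.15 | 0.87 | 0.89 | 0.91 | 0.94 |
| 70%; 0.05 | 0.86 | 0.94 | 1.00 | 1.12 |

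The ratio to truth runs from 0.8272/0.90 = 0.92 to 1.1248/0.90 = 1.25, and the sign turns on *d*. Starting time at the later of the first negative test and the first record gave 0.89 to 0.90 in all three settings. A wider set of assumed recording rates gave 0.72 to 1.96 times the rate in all repeat testers, with later entry within about 1% of that overall rate.

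**Step 3: trend.** Under the any-time rule, a record made in a later year also qualifies person-time in earlier years. Completeness is therefore a property of the man's whole record, not of a calendar year. With entry spread over 2009–2017, mean follow-up of 4 years before truncation, tests about every 0.75 years and a flat true hazard of 0.9 per 100 person-years (all assumed), the spurious rate ratio for 2015–2017 against 2009–2011 was:

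- recording constant at 30% or 50% per visit: 1.01 to 1.17, a false rise, since late entrants have had less time to acquire a record;
- recording doubling from 30% to 60% per visit: 0.95 at *d* = 1.0, 0.98 at *d* = 0.9, and 1.12 to 1.13 at *d* = 0.5.

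The wider set of assumptions gave 0.84 to 1.87. The trend, like the level, can be distorted either way.

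**The case against.** Several counter-arguments have weight.

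- **A diagnosis-time record is an inference.** No sentence says the qualifying record is made at diagnosis. It is tempting to cite Outcome 1, where "we will focus on HIV diagnoses where homosexual contact is identified as the route of transmission". That statement concerns the National HIV Registry, used there for a population prevalence estimate. The registry is not among the eligibility sources, which are data from the participating sites. It does not show that diagnosis creates a qualifying record. This stands, and so upward bias cannot be taken as established.
- **Completeness may be high.** Any of three indicators suffices, records are linked across services, incidence needs at least two tests, and 39 + 10 + 4 = 53 of the 59 health services are sexual health clinics, general practices with many gay and bisexual patients, or community-led services. The missing data noted under Covariates concern risk behaviour, not this indicator. If *s* is 0.99, the Step 1 inflation is below 1%. This limits the likely size; it does not remove the mechanism.
- **A constant bias largely cancels.** The primary aim is a temporal association estimated as a rate ratio. This is right, and only variation by calendar period threatens it. Step 3 shows that such variation can arise even when recording practice does not change.
- **The article is condensed.** A fuller document might date the indicator. But the article states both the entry rule and the time origin, and the difficulty lies in their combination.

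A reader might also compare one year at 80% completeness with another at 90%, get 0.8/0.9 = 0.89, and infer an 11% false decline in favour of the study hypothesis (or 22% from 0.7/0.9 = 0.78). That calculation does not fit the rule, because later records back-fill earlier person-time.

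**Conclusion.** The point holds as a design weakness of unknown sign and size. The stated rules let eligibility for the incidence analysis depend on records made at or after HIV diagnosis. They also count time from before a man qualified. Incidence is overstated if diagnosis or HIV care often creates the record, and understated if it seldom does.

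The document supplies neither completeness nor its course over time. The simulated ranges (level 0.72 to 1.96, late against early 0.84 to 1.87) show what assumed recording patterns can do; they are not estimates for this cohort. The documents do not support the claim that incidence is biased upward, or that the rule manufactures a decline. What they support is that the any-time rule leaves the primary outcome open to a distortion that covariate adjustment does not address and that can be removed with data already extracted.

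**What to change.** For the incidence analysis:

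1. Derive for each man the date of his first behavioural, identity or anal-swab indicator.
2. Start time at risk at the later of that date and the first negative HIV test.
3. Do not accept an indicator first recorded at or after the diagnosing test.
4. Report the any-time rule alongside as a sensitivity analysis, so that readers can see how far level and trend depend on it.

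The cost is one derived date per man. Some early person-time and some incident cases are lost, so precision falls slightly.
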